### Design

The study is designed as a randomized controlled trial with two parallel arms (see Figure 1). Forty patients will be randomized to either the treatment group (n = 20) or the control group (n = 20). The treatment group will receive EMDR in addition to TAU. The control group will receive TAU alone.

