### Outcome measures

The primary endpoint with respect to the efficacy of the standardized short-term EMDR intervention for CBP is the change in the intensity of back pain from T_0_ to T_1_ measured on a numeric rating scale (NRS 0–10, averaged over four weeks). The NRS for pain intensity has proven to be a reliable and valid instrument for assessing treatment effects in pain trials [55].

The secondary outcomes, which include distinct pain variables (mean pain duration, pain experience, and pain intensity at T_2_), medication intake, health-related quality of life (SF-12), anxiety and depression (HADS), dissociation symptoms (FDS-20), psychological resilience (RS-11), and somatization (SCL-90R subscale somatization), will be measured at all assessment points (T_1_ and T_2_).

In addition to the efficacy endpoints, we assess the peripheral and central modulation of pain (quantitative sensory testing, QST, and conditioned pain modulation, CPM) in all the patients to explore the differences in pain processing induced by the EMDR intervention. An overview of the primary and secondary outcomes is shown in Table 2.

**Table 2 T2:** Outcome measures

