### Assessment of safety

Serious adverse events (SAEs) will be documented and reported casuistically.

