### Sample size estimation

The sample size calculation is based on the primary efficacy endpoint: change in the pain intensity (numeric rating scale 0–10) after the intervention (T_1_). The expected effect size for our trial is derived from previous evidence about the effect of EMDR therapy for chronic pain patients.

The two controlled trials currently available are characterized by high effect sizes with Hedges’ g ranging from −1.12 [65] to −6.87 [66]. Based on this data, an effect size of at least 1.0 can be expected after ten sessions of treatment. A sample size of 17 patients in each group will have 80% power to detect an effect size of 1.0 using a t-test for independent groups with a 0.05 two-sided significance level. Based on comparable studies and our own experience with pain trials, we expect a 20% drop-out rate. Therefore, a total sample size of 40 patients is required for the study. The patients who are lost to follow up and/or non-compliant patients will be handled using an intention-to-treat procedure.

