### Statistical analyses

The data analysis will follow the evaluation standards for experimental study designs with control groups, using descriptive methods as well as inferential statistics. The data will be analyzed using an intention-to-treat approach. Because of the small sample size in the study, multiple imputation (the gold standard for handling missing values) is not appropriate. Therefore, only complete cases will be used in the final analysis. Dropouts, withdrawals and missing values will be analyzed in detail; different techniques will be used to assess them, and these techniques will be compared using sensitivity analyses. Descriptive statistics will be presented as the means and standard deviations for the continuous variables and absolute numbers and percentages for the categorical variables. The questionnaires will be processed in accordance with questionnaire manuals.

The differences between the change scores of the patient groups will be analyzed using independent t-tests. Moreover, potential negative effects will be reported descriptively (e.g., pain intensity after the trauma-focused intervention > pain intensity before the trauma focused intervention). Preliminary effect sizes will be estimated using Cohen’s d.

Pre-processing analyses and statistical analyses of quantitative sensory testing data will be performed according to the protocol used by Rolke et al. [63]. To quantify conditioned pain modulation, the pressure pain threshold before a phasic heat stimulus will be subtracted from the pressure pain threshold after the phasic heat stimulus. A negative value indicates an analgesic effect due to CPM [64].

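### The one printed example of a negative effect is a before-after pain increase in the EMDR arm only, with no minimum size; it cannot be interpreted without the same count under TAU

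*Protocol article*

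**What the plan says.** The Statistical analyses section of the protocol article says that possible negative effects are to be presented descriptively, and gives this example: "pain intensity after the trauma-focused intervention > pain intensity before the trauma focused intervention". The comparison is made around the trauma-focused intervention, and the Design section shows who receives that: "The treatment group will receive EMDR in addition to TAU. The control group will receive TAU alone".

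The same section says of the analysis set: "Therefore, only complete cases will be used in the final analysis". It then adds: "Dropouts, withdrawals and missing values will be analyzed in detail; different techniques will be used to assess them". The results are to be compared in sensitivity analyses.

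The Outcome measures section describes pain intensity as "measured on a numeric rating scale (NRS 0–10, averaged over four weeks". It is assessed in both arms at baseline (T0), two weeks after treatment (T1) and six months after treatment (T2). Under Sample size estimation the authors write that "we expect a 20% drop-out rate". The only other safety statement is under Assessment of safety: "Serious adverse events (SAEs) will be documented and reported casuistically".

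**The concern.** Back pain scores fluctuate. Some patients score higher at the second measurement than at the first whatever treatment they receive, and a criterion that counts any increase will pick them up. A before-after count in the treated arm alone cannot separate these patients from those whom the treatment made worse.

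This trial has a randomised TAU arm with the same pain scale at the same visits, so the background rate of worsening is available at no extra cost. The printed example does not use it. The article's own Discussion criticises earlier EMDR pain studies for lacking randomisation and adequate control groups, and an uncontrolled count of worsening has the same weakness.

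The criterion also needs a T1 value. A patient without one is neither worsened nor not worsened; that patient drops out of the count. What is at stake is the description of harm from a trauma-focused treatment, which could look worse or better than it is.

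**Working it through.** The plan gives no expected rate of worsening, so there is no figure of its own to reproduce on this point.

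**Inputs from the protocol article**
- 20 patients randomised per arm (Design).
- Expected drop-out 20% (Sample size estimation), so 20 × 0.80 = 16 completers and 4 without T1 per arm, if drop-out is equal in both arms.
- Pain on a 0 to 10 scale; criterion: after greater than before.

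**Assumptions, not in the documents**
- The change from T0 to T1 is normally distributed.
- Its SD lies between 1.0 and 2.5 points.
- Scores are recorded as whole points, so an observed rise means an underlying change above 0.5.

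**Step 1: chance of a rise with no true change.** P = 1 − Φ(0.5 / SD).

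**Step 2: chance of a rise with a mean improvement of one SD of change.** P = 1 − Φ((0.5 + SD) / SD) = 1 − Φ(1 + 0.5 / SD). One SD was chosen because the sample size assumes an effect size of 1.0; reading that as the mean improvement in the EMDR arm is a further assumption.

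| SD of change | No true change | Of 16 | Mean improvement of 1 SD | Of 16 |
|---|---|---|---|---|
| 1.0 | 0.309 | 4.9 | 0.067 | 1.1 |
| 1.5 | 0.369 | 5.9 | 0.091 | 1.5 |
| 2.0 | 0.401 | 6.4 | 0.106 | 1.7 |
| 2.5 | 0.421 | 6.7 | 0.115 | 1.8 |

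If the four-week average is recorded on a continuous scale, the two shares are 1 − Φ(0) = 50% and 1 − Φ(1) = 16%, whatever the SD.

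**Step 3: what the count can show.** In these scenarios fluctuation alone gives anything from about 1 to about 7 rises among 16 completers, depending on the SD and the mean change. An EMDR count of, say, 6 of 16 would be unremarkable if TAU also showed 6 of 16, and notable if TAU showed 1 of 16. The EMDR figure alone does not tell these cases apart.

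**Step 4: patients without T1.** Suppose 4 of 16 EMDR completers worsened, which is 25%. Among all 20 randomised, the share lies between 4/20 = 20% if none of the four missing patients worsened and (4 + 4)/20 = 40% if all did.

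**The case against.** The strongest reply is that the criterion is only an example, introduced as such and reported descriptively. No test or decision depends on it. The primary analysis already compares change scores between arms, so a mean worsening under EMDR would show against TAU, and nothing forbids the same count in the TAU arm. The SD of change is assumed, and zero mean change is the unfavourable case; with the benefit the authors expect, only about 1 to 2 of 16 would be flagged. Much reporting detail may also sit in the full protocol or the analysis plan.

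Most of this is fair, and it limits the point. It does not remove it. The authors chose to print one concrete criterion, and followed as written it gives an uncontrolled count. A between-group mean does not replace a count of individuals who worsened, because a favourable mean can coexist with a minority who got worse. That the flagged share moves from about 7% to 42% with the assumed benefit and SD is itself the reason why the TAU rate is needed.

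A reader might infer more than the text supports:
- **That this is the trial's whole definition of harm.** It is given as an example, and the statement on serious adverse events is not limited to one arm.
- **That treatment-related drop-outs will be missed.** The plan commits to analysing drop-outs and withdrawals. Stopping EMDR does not by itself mean a missing T1 value, and the 20% is drop-out from any cause. Only the count in question leaves these patients out.
- **That a particular threshold, such as 2 points, is required.** The documents give no basis for one. With no true change, 1 − Φ(1.5 / SD) still flags 16% to 27% for SDs of 1.5 to 2.5, so a threshold alone does not replace the control rate.
- **That case-by-case reporting of serious events is a defect.** With 20 per arm it is a normal choice; a table by arm is an optional preference.

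**Conclusion.** The point holds in a limited form. The only negative-effect criterion printed is worded for the EMDR arm, sets no minimum increase and cannot count a patient without T1. With no true change, roughly 5 to 7 of 16 completers (31% to 42%) would meet it by chance; with a mean improvement of one SD, roughly 1 to 2 of 16 (7% to 12%). These figures rest on normally distributed change, an assumed SD of 1.0 to 2.5 points and whole-point scores; on a continuous score the shares are 50% and 16%. That the count needs a control rate does not depend on the exact SD.

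The consequence is confined to how worsening is described and interpreted. The primary efficacy analysis is unaffected.

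**What to change.** - Restate the criterion as change in pain intensity from T0, and apply it identically to both randomised arms at T1 and T2.
- Report n/N per arm, the risk difference and its 95% confidence interval.
- If a minimum increase is used, the sponsor should fix it in advance and justify it.
- Within the drop-out analysis already promised, list withdrawals with reasons by arm next to this count, so that patients without a T1 value are visible.

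The pain scores are already collected in both arms, so no visits or patients are added. The cost is one table and recording the reason for each withdrawal.

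The intervals will be wide. With 16 completers per arm and 40% flagged in each, the normal approximation gives a half-width of 1.96 × √(2 × 0.40 × 0.60 / 16) = 0.34, or about 34 percentage points. The comparison cannot exclude a moderate excess of worsening, but it shows that uncertainty openly, which a one-arm count does not.

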**Methods/design:**

The study will recruit 40 non-specific CBP patients who have experienced psychological trauma. After a baseline assessment, the patients will be randomized to either an intervention group (n = 20) or a control group (n = 20). Individuals in the EMDR group will receive ten 90-minute sessions of EMDR fortnightly in addition to TAU. The control group will receive TAU alone. The post-treatment assessments will take place two weeks after the last EMDR session and six months later.

The primary outcome will be the change in the intensity of CBP within the last four weeks (numeric rating scale 0–10) from the pre-treatment assessment to the post-treatment assessment two weeks after the completion of treatment.

In addition, the patients will undergo a thorough assessment of the change in the experience of pain, disability, trauma-associated distress, mental co-morbidities, resilience, and quality of life to explore distinct treatment effects. To explore the mechanisms of action that are involved, changes in pain perception and pain processing (quantitative sensory testing, conditioned pain modulation) will also be assessed.

The statistical analysis of the primary outcome will be performed on an intention-to-treat basis. The secondary outcomes will be analyzed in an explorative, descriptive manner.

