**Secondary outcomes**	
**Pain dimensions**	• *Pain duration* (number of painful days in the last 4 weeks).
	• *Pain Experience Scale (SES)* measures the affective and sensory dimensions of pain [56].
**Medication**	• Change in medication intake.
**Disability**	• *12-Item Short Form Health Survey (SF-12)* measures health-related quality of life [57,58].
**Depression and Anxiety**	• *Hospital Anxiety and Depression Scale (HADS-D)*[59].
**Stress/ Trauma**	• *Change in Posttraumatic Diagnostic Scale levels (PDS)*[60]*.*
	• *Dissociation symptoms questionnaire (DES/FDS-20)* for assessment of dissociative symptoms [61].
**Somatization**	• *Somatization scores* of the SCL-90R subscale somatization (SCL-90R) [62].
**Somato-sensory function**	• *Quantitative Sensory Testing (QST)* for assessment of all relevant aspects of the somatosensory system including large and small fiber function as well as signs of central sensitization (dynamic tactile allodynia, punctate mechanical hyperalgesia) [63].
**Conditioned pain modulation**	*• Conditioned Pain Modulation (CPM)* paradigm for assessment of inhibitory pain modulating mechanisms [64]. Difference in pressure pain threshold before and after inducing CPM by a phasic heat pain stimulus will be measured.

Moreover, as part of the LOGIN study, all the participants in our study will be assessed for a shared core set of variables, including a comprehensive assessment of neuromodulators (plasma nerve-growth-factor, plasma endocannabinoid and lipid levels) and the functional and structural changes in functional neuroimaging (fMRI), before and after treatment (for further details, see [43]).

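### The formula for the conditioned pain modulation score and the rule for reading its sign contradict each other

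*Protocol article*

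**What the plan says.** The Statistical analyses section gives the score in words: "the pressure pain threshold before a phasic heat stimulus will be subtracted from the pressure pain threshold after the phasic heat stimulus". The following sentence gives its interpretation, with a literature citation: "A negative value indicates an analgesic effect due to CPM".

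The CPM entry in Table 2 (Outcome measures) describes a "paradigm for assessment of inhibitory pain modulating mechanisms" and adds: "Difference in pressure pain threshold before and after inducing CPM by a phasic heat pain stimulus will be measured". It therefore confirms that the test measure is a threshold and that the construct is inhibition, but it gives neither an order of subtraction nor a sign.

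On the role of CPM, the Outcome measures section says that it is assessed together with quantitative sensory testing (QST) "to explore the differences in pain processing induced by the EMDR intervention", and Table 2 lists it among the secondary outcomes. The abstract says of these: "The secondary outcomes will be analyzed in an explorative, descriptive manner".

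**The concern.** The two adjacent sentences give opposite instructions. Subtracting the earlier threshold from the later one gives a score that rises when the threshold rises. A pressure pain threshold is the pressure at which pain begins, so a higher threshold means less sensitivity to pain. Under the printed formula analgesia is a positive score, yet the printed rule calls a negative score analgesic.

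For a mechanistic outcome the direction is the finding: did inhibition improve or worsen with EMDR? An analyst who computes the score by the first sentence and reads it by the second would treat a patient with working inhibition as showing no analgesia, and a gain in inhibition in the EMDR arm as a loss. A two-sided test would give no warning, because it returns the same p-value whichever way the score is signed.

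**Working it through.** **Inputs**
- Order of subtraction, from Statistical analyses: score = threshold after − threshold before.
- Sign rule, from the next sentence of that section: negative = analgesic.
- Type of measure, from Table 2: a pressure pain threshold, not a pain rating.
- Construct, from Table 2: pain inhibition. Effective inhibition raises the pressure needed to cause pain, so after > before.
- Threshold values: the article gives none. Those below are assumed, in arbitrary units, and only illustrate the sign.

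**Step 1: the sign in general.** If after > before, then after − before > 0. This holds for every baseline and every size of rise. The stated sign (negative) is not reproduced by the stated formula.

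**Step 2: both orders of subtraction, with assumed values**

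| Before | After | After − before (as printed) | Before − after | What happened |
|---|---|---|---|---|
| 300 | 360 | +60 | −60 | threshold rose: analgesia |
| 300 | 300 | 0 | 0 | no change |
| 300 | 240 | −60 | +60 | threshold fell: more sensitive |
| 200 | 240 | +40 | −40 | threshold rose: analgesia |
| 400 | 480 | +80 | −80 | threshold rose: analgesia |

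The rule that negative means analgesic matches only the before − after column, which is not the order the article prints.

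**Step 3: the comparison between arms.** Suppose CPM is compared through change scores, as the Statistical analyses section describes for differences between the groups. Take an assumed arm whose mean threshold before the stimulus is 300 at both visits, and whose mean threshold after it is 330 at baseline and 360 post-treatment.
- Baseline score: 330 − 300 = +30.
- Post-treatment score: 360 − 300 = +60.
- Change: 60 − 30 = +30, a gain in inhibition.

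Under the printed sign rule, a move further from negative values reads as a loss.

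**Step 4: what does not change.** Multiplying every score by −1 turns a between-arm difference D into −D and leaves its standard error alone. The t statistic becomes −t. The absolute difference, the absolute value of Cohen's d and the two-sided p-value stay the same.

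**The case against.** **One of the sentences may be right.** This stands. Negative as analgesic is the correct reading of before minus after, and Table 2 does not settle the order. A reader might infer that the sign sentence is the mistake. The article does not support that, because the order of subtraction could equally be the slip. What it does show is that the two do not fit together.

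**The cited source may use a convention in which negative means analgesic.** That may be so, and the source is not available here. It would not repair the text, since the contradiction lies between two sentences printed in the article. The rule would also suit a pain rating, where inhibition lowers the number, but both places that define the measure name a threshold.

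**The consequence is conditional.** This also stands. A reader might infer that the CPM result will be reported backwards. That requires both sentences to be followed literally through scoring and reporting, and nothing shown indicates that the case report form or the code carries the conflict. The score is computed from the thresholds before and after the stimulus, so the direction can be recovered wherever these are kept. Nor does the article say that a positive value means facilitation.

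**CPM is a small part of the trial.** Largely right. A reader might infer that the mechanistic aim as a whole is compromised. It is not: the article also lists QST, plasma nerve growth factor, endocannabinoid and lipid levels, and functional neuroimaging. Secondary outcomes are exploratory and descriptive, and the primary analysis does not use CPM. This lowers the severity but does not remove the contradiction.

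**A journal article leaves detail to the full plan.** That would excuse a missing definition. Here both the formula and its interpretation are given, and they disagree.

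**Conclusion.** The point holds as an internal contradiction in the definition of a secondary outcome score. It follows from the printed formula and the meaning of a pain threshold, and it depends on no assumed number; the 300-to-360 example only makes the sign visible.

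The effect, if both sentences are applied as written, is a reversed verbal direction for every nonzero individual CPM score and for the between-arm comparison. The primary endpoint (change in pain intensity from baseline to two weeks after treatment) and the sample size do not involve CPM and are untouched. Severity is moderate: the error could turn the conclusion on a named mechanistic measure the wrong way round, but that measure is exploratory and the efficacy conclusion does not rest on it.

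**What to change.** Reconcile the two sentences in one of two ways:
- keep threshold after minus threshold before, and state that a positive value indicates analgesia; or
- define the score as threshold before minus threshold after, and keep the statement that a negative value indicates analgesia.

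Repeat the chosen order and sign in the CPM entry of Table 2, which at present gives neither. Check that the scoring code and the results report use the same convention; a test record with a known rise in threshold is enough to confirm the sign. The cost is one corrected sentence, a short addition to the table and a brief check of the code. No new data are needed, and the design and the primary analysis do not change.

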## Discussion

Although CBP is often accompanied by psychological trauma and posttraumatic stress symptoms, a specific trauma-focused approach for this subgroup of CBP cases has been a neglected issue to date. Eye movement desensitization and reprocessing, originally developed as a short-duration, high-efficiency treatment approach for posttraumatic stress symptoms, is a promising approach for treating CBP in patients who have experienced psychological trauma. The preliminary evidence suggests that EMDR treatment may benefit patients with medically unexplained somatic symptoms [54]. To date, several uncontrolled studies using EMDR have been conducted for a multitude of various pain syndromes [40,66-70]. These studies suggest that EMDR may be a safe and promising treatment option for chronic pain conditions.

However, most of the research conducted thus far has been preliminary in nature and characterized by small sample sizes, heterogeneous patient groups, the lack of randomization and the absence of adequate control groups. Moreover, to our knowledge, none of these studies have evaluated the efficacy of EMDR in patients suffering CBP. Thus, there is an urgent need for further exploration of the efficacy of EMDR for treating chronic pain patients using well-designed studies with standardized EMDR interventions of sufficient treatment length and adequate control groups. Accordingly, we designed this randomized controlled trial on the effects of EMDR treatment for non-specific chronic back pain patients who have experienced psychological trauma to determine whether a standardized short-term EMDR intervention reduces pain intensity in this subgroup of CBP patients. Because this is the first randomized controlled trial on this topic, the results of this study will encourage a more specific trauma-focused treatment approach, especially for the pain patients who have experienced psychological trauma.

However, although there is preliminary evidence that EMDR is effective and useful for the treatment of chronic pain, the underlying mechanisms remain unclear. Therefore, our core study will be supplemented by a comprehensive neurophysiologic and psychosocial assessment to explore these mechanisms of action.

Notably, the study is part of the LOGIN consortium study [41]. LOGIN comprises seven subprojects, including basic and applied research as well as preclinical and clinical projects utilizing a wide variety of research methods. As part of this consortium study, all the participants in our study will additionally be assessed for a shared core set of variables to investigate similar pathogenetic mechanisms. This approach enables us to expand our exploration of the underlying mechanisms by conducting a comprehensive assessment of systemic neuromodulators (plasma nerve-growth-factor, plasma endocannabinoid and lipid levels) and the functional and structural changes with functional neuroimaging (fMRI) before and after treatment and to explore the differences in pain processing induced by the EMDR intervention. This approach will be supported by the translational aspects of LOGIN. Thus, using the synergy of the different subprojects, the timely translation, implementation and dissemination of the results will be guaranteed.

The findings of this study might contribute to improvements in the treatment of patients suffering from CBP as well as to better understanding of the mechanisms of action underlying EMDR in chronic pain patients.
